Five brief intervention trials have been conducted with pregnant women in the USA [22-26]. Two trials were small (pilot) studies [23,25], with assessment and/or brief intervention procedures that were much longer in duration (1 to 2 hours) than the time available in antenatal care in the UK [23-25]. Four trials were based in obstetric settings [22-25], and three used specialist practitioners to deliver brief intervention [22,24,25]. Two trials included a single session of brief intervention, one of 10 to 15 minutes [26] and the other of 25 minutes in duration [23]. The former reported significant effects of brief intervention [26], whereas the latter reported reduced drinking in both the control and intervention groups [23]. Finally, one study found that women in antenatal care receiving brief interventions were significantly less likely than women receiving no treatment to have an infant with low birth weight or to suffer preterm labor problems, while another study found positive effects of brief intervention on prenatal drinking in women with higher initial rates of consumption [22,23]. Most recently, a trial of brief interventions in antenatal clinics in South Africa found that women who received a brief intervention had significantly greater reductions in scores on the Alcohol Use Disorders Identification Test (AUDIT) screening tool [27] by their third trimester, compared with women receiving assessment only [28]. Taken together, this evidence suggests that brief intervention is a promising approach for alcohol risk reduction in antenatal care. However, it is necessary to establish if evidence from the USA and elsewhere is applicable to a UK context with marked cultural and health-system differences.

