#### Follow-up

Six months after a baseline interview (during the third trimester), the project manager ascertains whether the participant has experienced a fetal loss or had pregnancy complications diagnosed since her first trimester. In either case, the participant will be excluded from follow-up data collection and will not be contacted. This information will be sought from the Regional Maternity Survey Office (RMSO; http://www.nepho.org.uk/rmso/) and the community midwife in order to minimize the risk of causing distress to the participant by inappropriate telephone contact. The RMSO is a publicly funded organization supported by clinical staff, which collects information from hospitals across the north of England to monitor health outcomes for mothers and babies. The project administrator contacts participants who still meet the criteria for inclusion in their third trimester to arrange a telephone interview with the project manager (GW). In the interview, the project manager will administer the 7-day TLFB questionnaire, the EQ-5D-3 L, and a NHS service use questionnaire. We will also check whether participant follow-up rates vary based on socio-economic profile and drinking status.

At 6 months after the due birth date of the participant, the project manager will again contact the RMSO to check whether the participant has experienced a stillbirth or loss after birth, and any such cases will be excluded from follow-up data collection without further contact. Birth outcome data (covering birth weight, gestational age at delivery, presence of congenital anomaly and fetal loss, or loss after birth if appropriate) will also be abstracted and recorded on a case report form. The project manager will then follow up eligible participants by telephone to ascertain longer-term follow-up rates. The screening and outcome measurement tools (the TLFB, EQ-5D-3 L & NHS service use questionnaires) will be re-administered, and open response questions will be asked about the acceptability of the instruments.

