### Sample-size considerations

This is a pilot trial and therefore a formal power calculation is not required. However, providing data for the power calculation of a definitive trial is an important function of a pilot study, and a minimum number of 30 participants per group is recommended to estimate a parameter for this purpose [47]. We therefore aim to screen 2,742 women to arrive at a sample of 60 providing data at the 6-month follow-up. This is based on an estimate from the UK Infant Feeding Survey 2005 [7] that 220 (8%) of those screened will screen positive. We expect 10% of these to be ineligible because of substance use [48] and 20% because of other exclusion criteria, leaving 70% (154) eligible for the study. We estimate, based on rates in a comparable study in the US [26], that 78% (n = 120) of this remainder will consent to enter the pilot RCT, with 60 participants in each of the intervention and control arms. This should provide data from at least 30 women in each group at follow-up, allowing for 33% attrition in the first wave [47] and 25% in the second wave (Figure 1). In this way, screening and intervention sample sizes will be sufficient to estimate the actual recruitment and retention rates for a UK sample of pregnant women recruited in antenatal care and provide data on the acceptability of study processes and outcome measures [47].

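### Ending follow-up for any complication found after enrolment selects on a possible intervention effect and leaves the retention denominator unsettled

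*Protocol article*

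**What the plan says.** The Follow-up section has the project manager check, six months after baseline, "whether the participant has experienced a fetal loss or had pregnancy complications diagnosed since her first trimester". The consequence is "In either case, the participant will be excluded from follow-up data collection and will not be contacted". Follow-up then continues for a reduced group: "The project administrator contacts participants who still meet the criteria for inclusion in their third trimester". At six months after the due date a second check covers stillbirth and loss after birth, and "any such cases will be excluded from follow-up data collection without further contact". The reason given for checking records and the midwife first is "in order to minimize the risk of causing distress to the participant by inappropriate telephone contact".

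Other sections bear on this:

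- **Randomization:** midwives were allocated before any woman was screened, without concealment.
- **Exclusion criteria:** pregnancy complications are a baseline exclusion.
- **Background:** one study of brief intervention in antenatal care found treated women "significantly less likely than women receiving no treatment to have an infant with low birth weight or to suffer preterm labor problems".
- **Measures, Baseline:** retention is one of the primary outcomes.
- **Sample-size considerations:** "This should provide data from at least 30 women in each group at follow-up, allowing for 33% attrition in the first wave", followed by 25% in the second wave. Progression is supported by retention of 67% and 75% at the two stages.
- **Economic evaluation:** utilities are to be collected from every participant, with EQ-5D at baseline and both follow-ups. NHS resource use comes from interview.

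**The concern.** The rule acts after midwives are randomized and women enrolled, on an event that the protocol's own evidence says the intervention may alter. If brief intervention prevents some complications, the women left for interview differ in kind between the arms, and randomization no longer protects the comparison among them. Ascertainment could also differ by arm, because the community midwife, who knows her allocation, is one of the two sources for the check.

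Drinking diaries, EQ-5D and service-use questionnaires come only from interviews that these women do not get. The Economic evaluation lists in-patient stays and pregnancy-related readmissions among the costs of interest, and women with complications are plausibly the ones who incur them. The pilot exists to supply variance estimates and to rehearse cost collection for a definitive trial of the same design, so that trial could inherit both the gap and the rule.

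Retention is also affected. The Sample-size section applies its rates to all 120 recruited women, whereas the Follow-up section speaks of ascertaining longer-term follow-up rates by telephoning those still eligible. The two readings give different answers on a primary outcome that drives the decision to proceed.

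**Working it through.** **Inputs from the document:** 2,742 screened, 8% positive, 70% of those eligible, 78% consenting, 60 per arm, attrition of 33% then 25%.

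**Input assumed:** the share x of recruited women excluded under the rule. The document gives no rate, so x runs from 5% to 25%, equal in both arms and applied once, before the first wave.

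**1. The plan's own chain reproduces.**
- 2,742 × 0.08 = 219.4 (stated 220)
- 220 × 0.70 = 154
- 154 × 0.78 = 120.1 (stated 120)
- 120 × 0.67 = 80.4
- 80.4 × 0.75 = 60.3, or 30.15 per arm (stated at least 30)

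The first-wave denominator in this chain is all 120 recruited women. The 75% applies to those retained at the first wave.

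**2. Effect of x.**
- A: 67% retention among still-eligible women, as a share of all recruited = 0.67 × (1 − x)
- B: response needed from contactable women if the excluded count as not retained and 67% of all recruited is required = 0.67 / (1 − x)
- C: number per arm at second follow-up if exclusions come on top of the stated attrition = 60 × (1 − x) × 0.67 × 0.75

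| x (assumed) | A | B | C |
|---|---|---|---|
| 0% | 67.0% | 67.0% | 30.2 |
| 5% | 63.7% | 70.5% | 28.6 |
| 10% | 60.3% | 74.4% | 27.1 |
| 15% | 57.0% | 78.8% | 25.6 |
| 25% | 50.3% | 89.3% | 22.6 |

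Under C there is almost no slack: 1 − 30/30.15 = 0.5%, so any larger excluded share takes the expected number below 30 per arm.

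**3. How selection could arise (all values assumed).** Let complications occur in 20% of control and 10% of intervention women, the difference being due to the intervention. Let maximum units average 8 in the 20% of women who would have a complication under control and 4 in the rest, with no effect on drinking.
- Full mean in either arm: 0.20 × 8 + 0.80 × 4 = 4.8
- Observed control mean: 4.00
- Observed intervention mean: (0.10 × 8 + 0.80 × 4) / 0.90 = 4.44

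The rule creates a difference of 0.44 units where none exists. If complications are equal at 20% and the same women are affected, the difference is zero, but both arms show 4.0 rather than 4.8.

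**The case against.** A reader might infer that the rule inflates retention. The document does not establish that. The sample-size chain runs on all 120 women and the progression rule refers to participants without restriction, so excluded women would count as not retained and the rate would fall. The wording about women who still meet the criteria describes whom the administrator telephones. The reference to follow-up rates among those still eligible is only ambiguous. What stands is that the denominator is unsettled.

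The attrition allowance may already cover these women. It is the only loss stated between 120 recruited and 60 with data, and the document does not say which losses it includes. On that reading, column C counts them twice. That objection stands, so column C is conditional.

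Not all follow-up data are lost. Birth outcomes, including fetal loss, are still to be abstracted from Regional Maternity Survey Office (RMSO) records. The Background evidence is a single study, and the same section says applicability to the UK has to be established. Only preterm labor problems clearly overlap the exclusion trigger, because low birth weight is known only at delivery. Between-arm tests are exploratory and no hypothesis is tested, so a distorted contrast here decides nothing by itself.

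These points lower the severity but do not remove the concern. The distress rationale plainly fits a loss. The article does not explain why it should cover every complication in a continuing pregnancy. The interview data are still lost, and the pilot's estimates are meant to be carried forward.

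**Conclusion.** The concern holds in a limited form, as a should-fix. The Follow-up section re-applies a baseline exclusion after randomization, on an event the intervention may change, and so loses drinking, EQ-5D and service-use data that the Economic evaluation wants from every participant. Selection bias is a risk, not a demonstrated fact. Its size depends on complication rates and drinking levels that the document does not give.

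Retention has two conflicting denominators. At an assumed 5% to 25% excluded, 67% among still-eligible women corresponds to 64% to 50% of all recruited, a gap of about 3 to 17 percentage points. If the excluded are counted as not retained, contactable women must instead respond at 70.5% to 89.3% to meet the first criterion. Numbers per arm fall to between 28.6 and 22.6 only if the exclusions are additional to the stated attrition.

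The text also leaves open whether a woman excluded for a complication at the first follow-up returns at the second, where the check names only stillbirth and loss after birth.

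**What to change.** - Compute retention and the progression criteria with all recruited women as the denominator. Because 75% is conditional on the first wave, state the second criterion also as a share of all recruited: 0.67 × 0.75 = 50.25%. Say whether protocol exclusions fall within the 33% and 25%.
- Report women not contacted under the protocol as a separate category, by arm and reason.
- State that RMSO birth outcomes, and service use where records hold it, are abstracted for every participant, including those not telephoned.
- Reconcile the complication exclusion with its distress rationale and with the aim of collecting utilities from every participant, so that a complication in a continuing pregnancy does not by itself end data collection unless that is justified. State whether women excluded at the first follow-up return at the second. Who may be contacted, and how, remains a clinical and ethical judgement.

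The cost is a small amendment, some extra record abstraction and possibly a few sensitive calls.

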#### Economic evaluation

The pilot study will rehearse how the relative costs and benefits of the intervention compared with the control group will be assessed from the perspective of the NHS in a definitive trial. It will also explore the appropriate use and application of data-collection instruments, to allow the economic analysis for a definitive trial to be structured.

This pilot study will test the collection of health-state utilities for each participant because a cost-utility analysis will be performed in the definitive trial. The main analysis will measure the incremental cost per quality adjusted life year (QALY) at the end of the trial follow-up period. QALYs will be based upon the responses to the EQ-5D-3 L, which is a standardized instrument with a three- level variance for use as a measure of health outcomes. Responses will be gathered at baseline and both follow-ups, and converted into QALYs using the area under the curve method [46].

To obtain the costs of the intervention, participating GP practices will be contacted about the type of room used for the delivery of intervention and any related booking costs. A case report form will be used to record the time for the alcohol counselor to book the intervention and to hold the intervention itself. The costs of intervention-related resource use will be obtained from each participating center or constructed based on the unit costs of health and social care (that is, the personal social services research unit). Within the pilot study, the completeness of data recorded from all sources and the appropriateness of the data-collection tools will be assessed.

Data will be collected at post-partum follow-up interviews regarding the use of NHS resources. Use of primary-care services includes antenatal and postnatal contact with midwives, GPs, practice nurses, community psychiatric nurses, dietitians, social workers and other uses relating to primary care (but not of the use of services specifically for treatment of alcohol misuse). Use of secondary care services includes non-intervention protocol, in-patient visits and stays, out-patient visits, visits to accident and emergency departments, readmissions relating to pregnancy, and other secondary care services (also excluding treatment of alcohol misuse).

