#### Exclusion criteria

Women are not eligible if they have pregnancy complications or have a multiple pregnancy; if they do not speak sufficient English to participate, or lack the cognitive capacity to understand the research and what is involved; if they have a history of substance use and/or alcohol dependence; or if they are experiencing a severe mental or physical illness likely to have an effect upon the intervention or on their ability to be followed up. Finally, women who are already participating in other alcohol-related research are excluded from the study.

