#### Brief intervention condition

Women in the intervention condition receive 5 minutes of simple structured alcohol advice delivered by the midwife, using a purposely designed brief advice tool (see Additional file 1). They retain the advice tool and receive a copy of *The Pregnancy Book*. If the midwife judges the reported rate of binge drinking or current alcohol consumption to be of concern, a referral is made to a drug and alcohol midwife for further assessment, advice, or treatment. These procedures take place at the booking appointment immediately after screening, obtaining written consent and completing the research questionnaire.

Women are then advised by the midwife that a member of the research team will contact them shortly by telephone to offer an appointment for brief alcohol intervention (manual available on request) with a trained alcohol health worker. This intervention takes 20 minutes, and is offered within 2 weeks of the initial consultation at the woman’s GP surgery housing the antenatal clinic.

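### The rehearsed costing takes an NHS perspective but excludes alcohol-treatment services, so it is incomplete, and biased if use of them differs by arm

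*Protocol article*

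**What the plan says.** All references are to the Protocol article.

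**Perspective and measure.** Economic evaluation says that relative costs and benefits "will be assessed from the perspective of the NHS in a definitive trial". It adds: "The main analysis will measure the incremental cost per quality adjusted life year (QALY) at the end of the trial follow-up period".

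**What is left out.** The same section lists the NHS use to be collected. Primary care ends with "other uses relating to primary care (but not of the use of services specifically for treatment of alcohol misuse". Secondary care ends with "other secondary care services (also excluding treatment of alcohol misuse". No reason is given for either exclusion.

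**What is costed for the intervention.** For rooms, "participating GP practices will be contacted about the type of room used for the delivery of intervention and any related booking costs". For staff time, a case report form is to "record the time for the alcohol counselor to book the intervention and to hold the intervention itself".

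**Where alcohol services enter the trial.** If the midwife is concerned about reported drinking, "a referral is made to a drug and alcohol midwife for further assessment, advice, or treatment". This wording stands under the brief intervention condition, and the control condition has the same rule.

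**The concern.** An NHS perspective means that NHS costs which follow from the choice of strategy are counted. Specialist alcohol care in pregnancy is such a cost, and it lies on the trial's own pathway, because both arms provide for referral to it. The plan removes it from both lists while still describing the perspective as that of the NHS.

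The decision to refer rests with the midwife. According to Randomization and Training, midwives are the randomized unit, know their allocation, and are trained in structured advice in one arm only until follow-up is complete. Women in the intervention arm are also offered a session with an alcohol counselor. Any of these could raise or lower use of specialist services in one arm.

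The comparison is also uneven. The counselor session in the intervention arm is costed. In the control arm, beyond verbal advice and a booklet, specialist referral is the only further alcohol-specific care described, and treatment arising from it would not be counted.

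What is at stake is the quality of the instrument carried forward. The third objective under Aim is to develop the methods and instruments for the economic evaluation. A rehearsal that leaves this item out cannot show how often such use occurs, whether women can report it, or whether it differs by arm.

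**Working it through.** The plan states no cost figure, so there is none to reproduce. The check has two parts.

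**1. The passages side by side**

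- Economic evaluation: NHS perspective, incremental cost per QALY.
- Economic evaluation: alcohol-misuse treatment excluded from primary and from secondary care.
- Control condition and Brief intervention condition: referral to a drug and alcohol midwife possible in both arms.
- Participant compliance: the case report form items named are receipt of brief advice, attendance at the intervention appointment, receipt of the intervention, and participation in follow-up. Referral is not among them.
- Economic evaluation: midwife contacts before and after birth are counted. A drug and alcohol midwife is a midwife, but may also be a service specifically for alcohol treatment. The text does not say which rule governs, so two interviewers could code the same contact differently.

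**2. Size of the omission**

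Let *c* be the mean NHS cost per user of alcohol-treatment services (taken as equal in both arms), and *p*<sub>I</sub> and *p*<sub>C</sub> the proportions using them in the intervention and control arms. Then

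reported incremental cost = full incremental cost − *c* × (*p*<sub>I</sub> − *p*<sub>C</sub>).

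- Equal use: *c* × 0 = 0, no error.
- Each percentage point of difference: 0.01 × *c* per woman.
- Assumed range of −10 to +10 points: −0.10*c* to +0.10*c* per woman, which includes zero.

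If the intervention raises use, the reported incremental cost is too low. If it lowers use, the reported figure is too high.

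On the scale of this pilot (Sample-size considerations), 60 women per arm are planned, with 60 × 0.67 × 0.75 = 30.15, about 30, reached at the second follow-up. One additional user in one arm shifts the mean cost per woman by *c*/60 = 0.017*c* if all are counted, or by *c*/30 = 0.033*c* among those reached.

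The documents give no value for *c*, *p*<sub>I</sub> or *p*<sub>C</sub>. No money amount can be derived from them, and the sign is open.

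**The case against.** **Use may be rare and balanced.** The referral rule is worded identically in both arms, and women are ineligible "if they have a history of substance use and/or alcohol dependence", which removes the likeliest users of treatment. The cost certain to differ by arm is the intervention itself, and that is costed. This stands as a limit on size. A reader might infer that alcohol treatment is the cost most likely to differ by arm, or that the incremental cost must be wrong. The documents support neither. They support only that a difference is plausible and would go unmeasured.

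**The exclusion may guard against double counting.** Because the counselor session is costed on its own form, a woman who also reported it as service use would be counted twice. That is a sound reason to exclude that session. It does not justify excluding all services for alcohol misuse, and the text does not offer it as the reason.

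**Some contacts may be captured as midwife contacts.** Referrals for assessment or advice could be counted that way, and the questionnaire itself is not shown. This shows that the boundary is unclear. It does not remove the written exclusion of treatment, which is a stated rule and not a detail left to a fuller document.

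**It is only a pilot.** The primary outcomes are feasibility rates, and the progression criteria contain no cost measure. That is correct. A reader might infer that the gap could not be repaired later, but the plan says that the appropriateness of its data-collection tools will be assessed, so an item could be added before the definitive trial.

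**Midwife time.** A reader might also infer that the 5 minutes of midwife advice go uncosted because the time form covers only the counselor. That does not follow: receipt of advice is recorded, its length is stated, and the costing refers to intervention-related resource use in general. Silence on training costs in a condensed article is not an error.

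**Conclusion.** The point holds in a limited form. The stated perspective and the two blanket exclusions do not fit together, and no reason is given. The rehearsed cost is incomplete for an NHS perspective. It is also biased, by *c* × (*p*<sub>I</sub> − *p*<sub>C</sub>) per woman, if use of alcohol services differs by arm. The error is zero if use is equal, and the documents fix neither its size nor its direction. The formula assumes the same mean cost per user in both arms; without that, the error is the difference between arms in mean alcohol-service cost per woman.

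Separately, the status of drug and alcohol midwife contacts is ambiguous and needs a rule.

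Nothing here affects the pilot's feasibility outcomes or its progression criteria. The consequence is a less informative rehearsal of the economic instrument, which is one of the pilot's stated objectives. The change is worth making because it is cheap.

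**What to change.** - Replace the two blanket exclusions with one that removes only the protocol-delivered counselor session, which is already costed separately.
- Add items on alcohol-service use, naming contacts with the drug and alcohol midwife, to the NHS service use questionnaire at both follow-ups. The Follow-up section already schedules that questionnaire at both; Economic evaluation mentions only the post-partum interviews, so the two should be aligned.
- State that drug and alcohol midwife contacts are recorded under the alcohol-service items and not again under general midwife contacts.
- Add a field to the booking case report form, in both arms, for whether a referral was made.
- Report referral and alcohol-service use by arm, descriptively.

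If the exclusions are to stay, the alternative is to give the reason and describe the perspective as a partial NHS one.

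The cost is a few form items and a slightly longer telephone interview. Care, randomization and sample size are unchanged.
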